#### Qualitative component

At the end of the intervention, a purposive sample of participants in the experimental group will be interviewed to include, as far as practicable, a range of sociodemographic factors, including age, ethnicity, education, marital status, and mobility. Semi-structured in-depth interviews will be conducted by one of the researchers in a mutually agreeable location. Topics that will be explored will include: what the intervention meant for the participant, any benefits derived from the intervention, interest in and barriers to continuing the exercises and ideas that would improve the intervention. Of particular interest are participants’ views of whether they were able to take steps towards achieving a desired activity and if successful, whether the skills learnt could be applied to another desirable activity. Interviews will last between 1.0 and 1.5 hours, be audio-recorded and fully transcribed. A constant comparison process will be used for each qualitative component; researchers will reflect on and discuss completed interviews and revise the question schedule accordingly to ensure a broad capture of new important information.

The research questions in the qualitative component of the study are evaluative in nature, emphasising and exploring issues of utility, feasibility and propriety [51]. After the first six participant interviews, theoretical sampling will be used to guide further recruitment and interviewing, to capture the stories of participants with potentially different experiences to challenge emerging themes. Recruitment will cease at data saturation when no new themes emerge from the interviews. It is anticipated that data saturation will be reached after approximately 20 participants have been interviewed. Each physiotherapist will be interviewed about their experience of delivering ACTIV. The interview will include questions about positive and negative aspects of the programme, suggestions for programme modifications and anything that would have assisted in the delivery of the intervention.

#### Adverse events

Every participant in the intervention and the control arm of ACTIV will be telephoned monthly by a research assistant, independent of the study and blinded to group allocation. The research assistant will have a comprehensive understanding of the meaning of adverse events in the context of this study. An adverse event is defined as any untoward medical occurrence in a participant that does not necessarily have a causal relationship with the study treatment [52]. They will note all events and establish whether the participant feels that the event is attributable to the intervention or not. A report of all adverse events will be collated by a senior research officer, who will report to the DMC monthly, to ensure that any significant increase in adverse events in the intervention group as compared with the control group can be assessed. Adverse events will be coded according to the Common Terminology Criteria for Adverse Events version 4.0.

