### Intervention - ACTIV

The Augmented Community Telerehabilitation Intervention (ACTIV) is a 6-month standardised programme delivered in the participant’s home, focusing on two functional categories: ‘staying upright’ and ‘using your arm’. Within each functional category there are standard exercises addressing key components of the defined function. For each component there are parameters to select and modify, allowing the programme to be individualised. The parameters that can be changed include the support received during an exercise, the number of exercises prescribed and the environment in which the exercise will take place. ACTIV will be delivered by a physiotherapist who has completed a training package that provides a) information on the rationale of ACTIV, b) a menu of exercises with guidelines for treatment selection, c) information on goal setting and d) information to facilitate patients in the transition to increased independence. Patient-centred goals will be set at the first home visit (assessment visit) and the physiotherapist will then select exercises and activities aimed at incremental attainment of these goals. The physiotherapists will have telephone and internet access to a consultant physiotherapist with expertise in this programme and in stroke rehabilitation, with who they can discuss any concerns/questions regarding provision of the programme.

ACTIV consists of four home visits (weeks 1, 2, 12 and 25), five telephone calls (weeks 1, 4, 8, 16 and 20) and text messaging (twice weekly for the first 10 weeks and once weekly for the following 16 weeks). Some people with stroke re-access services following discharge from formal therapy. No effort will be made to prevent the intervention group receiving additional care either publicly or privately.

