### Additional support

If the participant requests information about stroke-related issues beyond the exercise programme, the physiotherapist will have information sheets commonly in use, which will be provided by the Stroke Foundation (a not-for-profit organisation supporting and representing people with stroke in the community) and will be kept in the folder used by the physiotherapist for assessment forms and other paperwork. These can be provided as required. The participant can contact the physiotherapist at any stage if an adverse event occurs, if there is confusion about the programme and instruction, or if they are unable to perform the exercises.

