### Usual-care control group

Some people with stroke re-access services following discharge from formal therapy; no effort will be made to prevent the control group receiving additional care either publicly or privately. However, participation in physical activity will be ascertained during a monthly phone call by a research assistant, independent of the study and blinded to group allocation. Participants in the control group will undergo the three assessments from the blinded assessor at baseline, 6 and 12 months.

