#### Physical activity

During the adverse event phone call each participant in the study will also be asked about their physical activity participation, including involvement in other therapy. Participants will be asked if they are undertaking therapy or organised exercise (apart from this study), and if so, its frequency and duration.

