#### Adverse events analysis

The occurrence of adverse events will be reported by descriptive statistics only, as we lack sufficient power to test for these events, and strongly expect the number to be low due to the low-risk nature of the intervention.

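### The blinded monthly caller must ask about attribution to the intervention, which is liable to disclose the arm, and ACTIV participants have an extra route for reporting adverse events

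*Protocol article*

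**What the plan says.** In the protocol article, Adverse events, every participant in either arm is to be "telephoned monthly by a research assistant, independent of the study and blinded to group allocation". The next duty given to the same caller is: "They will note all events and establish whether the participant feels that the event is attributable to the intervention or not".

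Under Physical activity, the same call has a second topic: "Participants will be asked if they are undertaking therapy or organised exercise (apart from this study), and if so, its frequency and duration".

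Additional support, which describes the ACTIV programme, adds: "The participant can contact the physiotherapist at any stage if an adverse event occurs". Intervention - ACTIV schedules four home visits and five telephone calls with that physiotherapist, plus text messages. For the other arm, Usual-care control group describes the same monthly call and says: "Participants in the control group will undergo the three assessments from the blinded assessor at baseline, 6 and 12 months". It mentions no study physiotherapist.

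Adverse events then has a senior research officer collate all events and report monthly to the DMC, so that "any significant increase in adverse events in the intervention group as compared with the control group can be assessed". Adverse events analysis limits the final reporting: "The occurrence of adverse events will be reported by descriptive statistics only, as we lack sufficient power to test for these events".

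**The concern.** There are two separate weaknesses in how the safety comparison is fed.

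**Blinding of the caller.** The article gives the caller a property (unaware of allocation) and a task (asking whether the intervention caused the event) that work against each other. A participant who has had home visits and exercises can answer 'yes' or describe the programme. A usual-care participant may say that there was no intervention to blame. Once the arm is known, the caller's probing, wording and decision to record can differ by arm in later months. The answers on other therapy and exercise, which describe co-intervention in a trial that restricts it in neither arm, come from the same conversation.

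**Unequal routes.** Only the ACTIV arm has a clinician to whom participants may bring an adverse event at any time. If such events join the count, ACTIV has two sources and usual care one.

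At stake is how the DMC reads the monthly by-arm report. Few events are expected and no formal test is planned, so a handful of extra ACTIV reports could look like harm, or a real excess could be put down to reporting.

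**Working it through.** No figure in the article tests this point, so the check sets the sections side by side and then gives an illustration.

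**1. Can the caller stay blind?**
- Adverse events says that the caller is blinded.
- The same section says that this caller asks about attribution to the intervention.
- The arms differ visibly to the participant (visits, calls and texts against usual care), so the participant knows the answer.
- A 'yes', or talk of the exercises, identifies ACTIV. A plain 'no' fits either arm. The question arises only when an event is reported.
- No section says how blinding is kept when the question is put.

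Disclosure is therefore a foreseeable risk, not a certainty. It carries over to later months if the same assistant calls again or sees earlier notes. The article does not say, so this is an assumption. The activity question adds to the risk, because asking about therapy outside the study invites ACTIV participants to mention what they receive inside it, whether or not an event occurred.

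**2. Are the event sources equal?**

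| Source | ACTIV | Usual care |
|---|---|---|
| Monthly call | yes | yes |
| Three blinded assessments | yes | yes |
| Physiotherapist, at any time, for adverse events | yes | none described |

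**3. Does the extra source enter the comparison?** The article describes event capture through the monthly call, followed by a report of all events. It does not say whether events told to the physiotherapist are included.

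**4. What could pooling do?** Suppose true event rates are equal. Let c be the share of events caught by the monthly call in either arm, and e the share of the missed events that reach the report through the physiotherapist. Then

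apparent ACTIV-to-control ratio = [c + (1 − c)e] / c.

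The values of c and e are assumptions; the article gives neither.

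| c | e = 0 | e = 0.25 | e = 0.50 |
|---|---|---|---|
| 0.60 | 1.00 | 1.17 | 1.33 |
| 0.75 | 1.00 | 1.08 | 1.17 |
| 0.90 | 1.00 | 1.03 | 1.06 |

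For example, (0.60 + 0.40 × 0.50) / 0.60 = 0.80 / 0.60 = 1.33. With e = 0, meaning that physiotherapist reports stay out of the comparison, the ratio is exactly 1.00.

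**The case against.** The strongest reply is that the only event capture the article describes is a monthly call, identical in both arms. The sentence about contacting the physiotherapist stands under support for the participant, beside confusion over instructions and difficulty with the exercises. It does not describe safety data collection. The structured telephone calls and follow-up visits cover progress, satisfaction, exercise performance and barriers, not the elicitation of events. On that reading the arms are already compared on a common source. Call scripts and event-form fields may also sit in the fuller protocol.

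Much of this stands, and it rules out three stronger readings that a reader might infer.

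- **That the safety comparison is biased.** This would need physiotherapist reports to enter the count, or the extra contacts to prompt more reports in the call. Neither is stated.
- **That the arm is revealed at the first event.** A 'no' fits either arm, and the same words can be used in both.
- **That ACTIV has 2.5 times as many occasions to report.** That figure comes from 6 monthly calls + 4 visits + 5 calls = 15, against 6. It assumes calls over six months only; if they run for 12 months the same sum is (12 + 9) / 12 = 1.75. It also leaves out the shared assessments and counts contacts not described as eliciting events. It does not measure ascertainment.

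What the reply does not remove is the first weakness. Giving a blinded caller the attribution question is a stated procedure that works against a stated property, not a detail left to another document. The word 'all' in the DMC report also leaves a real ambiguity. Pooled physiotherapist reports make capture unequal, while omitted ones mean that events known to trial staff may be absent from a report described as complete.

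**Conclusion.** The point holds in a limited form and should be corrected. The attribution question is liable to disclose allocation to a caller described as blinded, which can affect later event recording and the physical-activity data from the same call. The by-arm DMC comparison is open to ascertainment bias if events reported to the physiotherapist are pooled with those from the monthly call.

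Neither the size nor the fact of a bias can be derived from the article. Extra reporting would tend to raise the ACTIV count. The range of 1.00 to 1.33 rests wholly on assumed capture rates. The conclusion on blinding assumes that the caller, or the caller's notes, carry over from month to month.

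A reader might extend the point to efficacy. The article does not support that: a separate blinded assessor collects the outcome measures, including the primary SIS physical subcomponent, and the caller is not said to share information with that assessor. The final safety analysis is descriptive, so the consequence lies in how the DMC and readers interpret event counts.

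**What to change.** 1. Use one neutral script in both arms, with the same words and order, including the activity question. It could open by asking participants not to mention their study group.
2. Have the blinded caller record events only, without asking about attribution.
3. Have the senior research officer, who already collates the events, obtain the participant's view on attribution afterwards. This person will learn some allocations and should not pass them to the caller or the outcome assessors.
4. Add a field to the event form for the source of the first report: monthly call or physiotherapist.
5. State that the between-arm comparison, for the DMC and in the final tables, uses events from the common monthly call. Give the DMC the physiotherapist-reported events in a separate listing, so that no exercise-related harm is hidden by their exclusion from the comparison.

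The cost is a short second contact for the few participants with events, one form field and a revised script. No new staff are needed. A neutral script lowers the risk of disclosure through the activity question but cannot remove it, so the report should describe the caller's blinding with that caution.

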#### Physical activity

During the adverse event phone call each participant in the study will also be asked about their physical activity participation, including involvement in other therapy. Participants will be asked if they are undertaking therapy or organised exercise (apart from this study), and if so, its frequency and duration.

### Data analysis

#### Quantitative analysis

The difference between the two groups in mean changes in the primary outcome between 6 months and baseline will be obtained using analysis of covariance, adjusting for baseline, and accounting for the site using random effects. Secondary analyses will examine all efficacy outcomes over time in a mixed-effects model with centre- and patient-associated random effects. Demographic and other covariates will be assessed for inclusion in the regressions if they differ across treatment arms by more than one pooled SD. They will be retained for adjustment purposes if they reach a significance threshold of 0.1 in the presence of the treatment effect and also in the presence of treatment effect and all such covariates. Trend analyses will be performed by estimating the interaction between treatment arms and piecewise linear functions of the true assessment time. Observations with missing outcome data will be deleted but partial outcome data will be retained in the case of secondary outcomes. Multiple imputation will be used for the production of final results, should covariate values be used for adjustment. Survival analysis of attrition will be used to assess whether differential attrition is extant, and the results used to inform the discussion. Primary analyses will be carried out on the basis of intention to treat. No interim analysis for efficacy will take place.

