### Study sample

#### Sample size

Sample size computations are based on a 5% per comparison significance level and a two-tailed critical region. Due to the variation in response to physiotherapy intervention after stroke a conservative approach has been taken with the assumption that there will be no correlation between baseline measures and final outcome. Two previous studies [36,37] have indicated consistent baseline SDs for the physical function subcomponent of the SIS, for a pooled baseline SD of approximately 21.7. A naïve combination of the clinically important differences (CID) from Lin and colleagues in 2010 [36], based on a geometric mean of the elements, yields a CID for the SIS physical function subcomponent score of 5.3, corresponding to an effect size of about 0.25. In their rehabilitation study, Marsden and colleagues 2010 [37] obtained standard errors for the mean differences in measurement, of 9.5 and 6.6 for their control and treatment groups, respectively. Using these values, 38.4 participants per arm will be required to detect the target effect size with 80% power, based on the appropriate *t*-distribution for the difference of two such changes from baseline. A total sample size of 96 will be required, allowing for an attrition rate of 20% over the 12-month research period. With these numbers, the probability is approximately 80% that the study will detect a treatment difference, if the true difference between the changes in ACTIV and usual care control group is at least 5.4 points in the physical subcomponent of the SIS3.0.

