### Randomisation

Randomisation will occur after the baseline assessment and participants will be assigned to one of two groups, ACTIV or usual care control. Randomisation will be stratified by centre (four locations) with recruitment targets of 32 participants from each of the North Island centres and 16 from each of the South Island centres, commensurate with the number of stroke admissions expected in each location. Stratified block randomisation will be used according to geographic centre and baseline mobility. Baseline mobility will be decided by the FAC: either ‘less mobile’ if they have a level of five or below or ‘more mobile’ if they have a level of six. Given the small numbers, random block sizes will be used according to a plan that ensures, according to simulations, a probability smaller than 0.1% that balance will be broken across strata by four participants or more. The randomisation software will be coded and tested by the study statistician, then handed over to a third independent party for random number generator seeding, execution of allocation, and day-to-day management of the randomisation. The recruiters, assessors and personnel involved in data management and analysis will be blinded to treatment assignment.

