### Primary outcome

The primary outcome measure is the physical function subcomponent of the SIS 3.0. [40]. The SIS 3.0 consists of 59 questions divided into eight domains; strength, hand function, mobility, activities of daily living, emotion, memory, communication and social participation. The four physical domains (strength, hand function, mobility and activities of daily living) can be summed to generate the physical subcomponent score. This is reported as a normalised summary score, has excellent test-retest reliability with interclass correlation (ICC) of 0.98, and the SIS has been shown to be responsive to change in this population [41]. Rasch analysis of the SIS indicates that the items are uni-dimensional with an excellent range of item difficulty [40].

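### The primary ANCOVA omits baseline mobility, one of the two randomisation stratifiers; if mobility predicts outcome beyond baseline SIS, the test is conservative and some power is lost

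*Protocol article*

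**What the plan says.** Three statements in the protocol article bear on this.

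- **Randomisation section.** "Stratified block randomisation will be used according to geographic centre and baseline mobility". The mobility stratum has two levels: "Baseline mobility will be decided by the FAC", with level 5 or below called less mobile and level 6 more mobile. The recruitment targets are "32 participants from each of the North Island centres and 16 from each of the South Island centres", giving 96 participants in 4 x 2 = 8 strata. The block plan is meant to keep the chance of an imbalance of four or more participants below 0.1%.
- **Quantitative analysis section, primary model.** The change in the SIS physical score from baseline to 6 months is compared by ANCOVA, "adjusting for baseline, and accounting for the site using random effects". Mobility is not named. The secondary mixed models are described with centre and patient random effects, again without mobility.
- **Quantitative analysis section, covariate rule.** "Demographic and other covariates will be assessed for inclusion in the regressions if they differ across treatment arms by more than one pooled SD". A candidate is then kept only if it passes a 0.1 significance threshold.

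The Primary outcome section is also relevant: "The four physical domains (strength, hand function, mobility and activities of daily living) can be summed to generate the physical subcomponent score". The baseline score in the model therefore already carries some mobility information.

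**The concern.** One stratifier is carried into the analysis and the other is not. When allocation is balanced on a prognostic factor, chance imbalance in that factor no longer adds to the sampling error of the treatment difference. If the model leaves the factor out, its variance stays in the residual, and the reported standard error describes more uncertainty than the design leaves. Confidence intervals are then too wide and the test runs below its nominal level.

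The covariate rule makes this worse, because it admits only variables that are imbalanced between arms. At stake is efficiency in a trial planned for 80% power with no margin. Bias and false-positive inflation are not at stake.

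**Working it through.** **1. The plan's own figure.** Inputs from the Sample size section: "5% per comparison significance level and a two-tailed critical region"; target difference 5.3 points; variability of change 9.5 and 6.6 in the two groups; 20% attrition. The stated result is reproduced when 9.5 and 6.6 are used as SDs.

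- Sum of variances: 9.5² + 6.6² = 90.25 + 43.56 = 133.81 (root mean square SD 8.18).
- Normal approximation: n = 133.81 x (1.9600 + 0.8416)² / 5.3² = 37.4 per arm.
- Noncentral t with 2n - 2 df: 38.37 per arm. The plan says "38.4 participants per arm will be required to detect the target effect size with 80% power".
- Total: 2 x 38.4 / (1 - 0.20) = 96.

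The stated size reproduces, so nominal 80% power is the reference below.

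**2. Can the covariate rule restore mobility?** Assume 48 per arm and half of participants in each mobility stratum (SD 0.5). A four-participant imbalance, 26 versus 22, is (26 - 22)/48 = 0.083, or 0.083/0.5 = 0.17 SD. One SD needs a difference in proportions of about 0.5, that is about 36 versus 12. Stratified blocking rules that out in practice.

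**3. Effect on standard error and type I error.** Let R2 be the share of the variance left after baseline SIS and site that FAC stratum explains. With balance on the stratum:

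- model SE / true SE = 1/sqrt(1 - R2)
- type I error = 2 x [1 - Phi(1.96/sqrt(1 - R2))]

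**4. Effect on power.** Take a noncentrality of 1.9600 + 0.8416 = 2.8016 for nominal 80% power.

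- Mobility omitted: Phi(0.8416/sqrt(1 - R2)). The estimate is more precise than the model credits, so power is slightly above 80%.
- Mobility included: Phi(2.8016/sqrt(1 - R2) - 1.96).

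The documents do not give R2, so the range is assumed:

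| R2 | SE ratio | Type I error | Power, omitted | Power, included | Gain (points) |
|---|---|---|---|---|---|
| 0 | 1.00 | 5.0% | 80.0% | 80.0% | 0 |
| 0.02 | 1.01 | 4.8% | 80.2% | 80.8% | about 0.5 |
| 0.05 | 1.03 | 4.4% | 80.6% | 82.0% | 1.4 |
| 0.10 | 1.05 | 3.9% | 81.2% | 84.0% | 2.7 |
| 0.20 | 1.12 | 2.8% | 82.7% | 87.9% | 5.3 |

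At the 5.4-point difference of the closing power statement, with 38.4 per arm, the same formulas give 83.1% versus 84.3%, 83.7% versus 86.2% and 85.1% versus 89.9% for the last three rows.

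**5. Simulation check.** Set-up: sites of 32/32/16/16; blocks of 2 or 4 within site and mobility; 20% random loss; equal mobility strata; correlation 0.5 between mobility and baseline; residual SD 8.18; 1,000 to 1,500 runs per scenario. With random site, a true difference of 5.4 and a site ICC of 0.08, power without versus with mobility was:

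- no mobility effect beyond baseline: 77.8% versus 77.9%
- effect of 0.5 residual SD: 78.8% versus 80.4%
- effect of 1 residual SD: 74.2% versus 80.3%

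Monte Carlo error on power is about 1.3 points, so only the last gap is clear of noise. These figures are not directly comparable with the table: here the mobility variance is added to the residual SD of 8.18, whereas the table holds the total residual variance fixed. Under the null, rejection at the 1 SD effect was 4.7% and 4.0% without mobility (site ICC 0.01 and 0.08), with a Monte Carlo error of about 0.6 points. Conservatism is therefore milder than the closed form suggests, as expected when loss and incomplete blocks make balance imperfect.

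**The case against.** **The size may be near zero.** The protocol gives no figure for what FAC predicts beyond the baseline score, and that score includes an SIS mobility domain. With equal strata and an SD of 8.18, R2 = 0.20 needs a difference between strata, after baseline adjustment, of 2 x 8.18 x sqrt(0.20) = 7.3 points, more than the 5.3-point target. This stands: the upper end of the range is demanding, and the standard error claim must be conditional.

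**An article condenses.** A fuller plan may list mobility among the covariates, and that would answer the point. But the article names the adjustment terms of the primary model and gives a rule for further covariates. Followed as written, the two together leave mobility out.

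**Stronger readings.** A reader might infer that the benefit of stratifying is lost altogether, and so set adjusted power against a flat 80%. That overstates the gain: the unadjusted estimate still benefits from balance, and only its reported standard error fails to credit it. A reader might also infer that four centres modelled as random make the treatment analysis unreliable. The site variance is indeed poorly estimated: in simulation it came out as zero in 53-54% of runs at a true ICC of 0.01 and 23-29% at 0.08. But allocation is blocked within centre, and random-site and fixed-site standard errors of the treatment effect agreed within about 1% (1.871 versus 1.880; 2.044 versus 2.056), with similar rejection rates.

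**Conclusion.** The point holds as a modest efficiency and alignment defect. The primary model as written omits a stratification factor, and the covariate rule cannot bring it back. If FAC stratum explains 5% to 10% of the variance left after baseline SIS and site, the model standard error is about 3% to 5% too large, the nominal 5% test runs at about 4.4% to 3.9%, and 1.4 to 2.7 points of power are forgone. At 20% these become 12%, 2.8% and 5.3 points; at zero there is no loss.

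The figures assume close balance on mobility in the analysed set, equal arms and a normal approximation; imperfect balance makes them smaller. The error is conservative and the treatment estimate is unbiased, so the validity of a positive result is not in question. The documents do not show that the standard error is too large as a matter of fact, nor that the handling of site is a defect.

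**What to change.** Name the FAC mobility stratum (level 5 or below versus 6) as a prespecified fixed covariate in the primary ANCOVA, alongside treatment, baseline SIS physical score and site. State that it is exempt from the one-pooled-SD rule and the 0.1 retention threshold, and carry the same term into the secondary mixed models. Centre may stay random or be made fixed.

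The cost is one line of analysis wording and 1 df of about 75. FAC level is needed to randomise, so no new data are required. If mobility proves unrelated to outcome, almost nothing is lost (77.8% versus 77.9% in the simulation). The Trial status section says recruitment had only just begun, so from that position the change could be made before any unblinded outcome data were seen.

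### The covariate rule needs a between-arm gap of one pooled SD, so it practically never adds to baseline SIS and site, and it keeps the mobility stratum out of the model

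*Protocol article*

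**What the plan says.** The Quantitative analysis section makes the primary analysis an analysis of covariance of change in the SIS physical subcomponent at 6 months. It adjusts for the baseline value and takes site as a random effect. Both terms are unconditional.

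Further covariates face two conditions in sequence. The first is on imbalance: "Demographic and other covariates will be assessed for inclusion in the regressions if they differ across treatment arms by more than one pooled SD". The second is on association with the outcome: "They will be retained for adjustment purposes if they reach a significance threshold of 0.1 in the presence of the treatment effect". The second must be met again when all such covariates are in the model together. The article gives no other route for a further covariate.

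The Randomisation section stratifies by centre and by baseline mobility, with FAC level six as more mobile and level five or below as less mobile. Mobility is not named in the analysis model.

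**The concern.** The rule reads as protection against chance imbalance. In a trial of this size a gap of one full SD between randomised arms is so rare that the rule is in effect switched off. Three things follow.

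- Moderate imbalances, which can occur and can move the estimate, are left alone.
- Covariates that predict the outcome are shut out when they are balanced, although adjusting for them would still tighten the estimate. Prognostic strength is the useful criterion, and imbalance is a poor stand-in for it.
- The mobility stratum was judged important enough to stratify on. Stratification holds it close to balance, so it is among the variables least able to pass. If mobility predicts the outcome, leaving it out gives standard errors that do not reflect the design and tend to be too wide.

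The rule is also not limited to baseline variables. A variable measured after randomisation, such as the other therapy or exercise recorded in the monthly calls, could differ by a full SD because treatment changed it. That would be the wrong reason to adjust.

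**Working it through.** **Inputs, all from the Sample size section**
- Test: "Sample size computations are based on a 5% per comparison significance level and a two-tailed critical region".
- Numbers: "38.4 participants per arm will be required to detect the target effect size with 80% power" and "A total sample size of 96 will be required, allowing for an attrition rate of 20% over the 12-month research period".
- Target difference: 5.3 points.
- Variability: "standard errors for the mean differences in measurement, of 9.5 and 6.6 for their control and treatment groups, respectively". These reproduce the plan's figure when used as SDs of change, and they are used that way here.
- Equal allocation, 48 per arm, is inferred from the equal number per arm. No ratio is stated.

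**Reproducing the plan's figure**
- Pooled SD = sqrt((9.5² + 6.6²)/2) = 8.18.
- Two-sample t-test, noncentral t, two-sided 5%, 80% power, difference 5.3: 38.4 per arm.
- Attrition: 2 × 38.4 / (1 − 0.20) = 96. The plan's figures are reproduced.

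**Chance of passing the imbalance test**

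In SD units, the standard error of a difference in covariate means is sqrt(2/n), so one SD equals sqrt(n/2) standard errors. The chance of exceeding it is the two-sided t tail on 2n − 2 degrees of freedom.

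| Per arm | SE (SD units) | One SD in SEs | Chance, one covariate | Chance, any of 20 independent |
|---|---|---|---|---|
| 48 | 0.204 | 4.90 | 4.0 in 1,000,000 | 0.008% |
| 38.4 | 0.228 | 4.38 | 3.8 in 100,000 | 0.08% |

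The second row assumes that loss to follow-up does not itself create imbalance. For binary covariates at 48 per arm, exact enumeration gives at most about 8 in 1,000,000 (prevalence 0.5).

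**What the rule leaves unadjusted**
- A 0.5-SD gap at 48 per arm is 0.5/0.204 = 2.45 standard errors. A gap at least that large arises about 1.6% of the time for any one covariate, and the rule ignores it.
- Assume such a covariate correlates 0.3 to 0.5 with the outcome change after baseline adjustment. The estimate then shifts by 0.5 × 0.3 × 8.18 = 1.2 points to 0.5 × 0.5 × 8.18 = 2.0 points, against a target of 5.3.

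**Precision forgone (illustration)**

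The documents do not say how much residual variance further covariates explain, so a range is shown. The residual SD is taken as 8.18 × sqrt(1 − share), with 38.4 per arm and a 5.3-point difference.

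| Share explained (assumed) | Residual SD | Power |
|---|---|---|
| 0% | 8.18 | 80% |
| 5% | 7.97 | 82% |
| 10% | 7.76 | 84% |
| 25% | 7.08 | 90% |

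A 10% share is worth 1/0.9 = 1.11, or about 11% more participants. Spending three degrees of freedom on covariates that explain nothing lowers power by less than 0.1 percentage point.

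**The case against.** The best defence is that the important adjustment is already fixed. The baseline score of a scale with a quoted test-retest ICC of 0.98 is plausibly the strongest predictor available, and it enters unconditionally, as does site. A rule that almost never operates leaves a valid, pre-specified, baseline-adjusted analysis. A named covariate list is also something a condensed article may leave to an analysis plan that is not shown. All of this stands, and it limits the harm. It does not rescue the rule, because the article states the rule and the rule is what is criticised.

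A reader might infer more than the document supports:

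- **That useful prognostic adjustment is ruled out.** It is not. Only adjustment beyond baseline SIS and site is affected.
- **That outcome-driven selection threatens type I error.** A first condition met less than 0.1% of the time, even across 20 covariates, cannot also leave a live post hoc choice. This would change if one standard error had been meant, because the condition would then be met about 32% of the time per covariate. The text says SD.
- **That selection would be unblinded.** The Randomisation section blinds those handling and analysing data. The Data monitoring section allows only partial unblinding of the study statistician.
- **That the multiple-imputation provision is dead.** It applies if covariate values are used for adjustment, and the baseline score could count as one.

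The scope is also unclear. The rule follows the sentence on secondary analyses and refers only to the regressions in general. If it covers the secondary models alone, the primary model still omits the mobility stratum.

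**Conclusion.** The point holds in limited form. For randomised baseline covariates the rule is practically inert: one pooled SD is 4.9 standard errors at 48 per arm and 4.4 at 38.4. It therefore gives no working protection against moderate imbalance, and it cannot admit the FAC mobility stratum. Validity is not in question.

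The loss is some precision, together with standard errors that ignore a stratification factor. The size of that loss rests on assumptions from outside the documents. A rise in power from 80% to 84% needs added covariates to explain 10% of residual variance, and nothing in the article shows that age or any other variable does so once baseline SIS is in the model. The 1.2 to 2.0 point shift likewise depends on an assumed correlation and on an uncommon imbalance. The case for change is that it costs almost nothing and makes the analysis match the design.

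**What to change.** Delete both conditions. State the primary model as baseline SIS physical score, site (random effect as planned), FAC stratum as a fixed covariate, and at most one or two further prognostic variables already collected at baseline, such as age. Name them before by-arm outcome data are seen, restrict them to variables measured before randomisation, and select nothing on baseline imbalance or outcome p-values. Say whether the same list applies to the secondary mixed models. Report the model with baseline SIS and site only as a sensitivity analysis.

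The cost is a change of analysis wording and about two or three degrees of freedom. No new data are needed: FAC level is required for randomisation, and age is needed for eligibility.
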